##### Child development

Child's development was measured at different periods:

At 6 months of age the Home Observation for Measurement of the Environment was conducted [45]. At 18 months, the language of the child and parental stress (Nijmeegse Ouderlijke Stress Index (NOSI)) were measured [46]. At the second birthday, the Child Behavior Checklist, Harsh Parenting and questions about raising the child were addressed[47].

##### Child abuse

Data about prevalence of child abuse were obtained from a maltreatment reporting agency where both professionals and the general public can report cases (Advies & Meldpunt Kindermishandeling) [48]. A contact person from this agency was asked whether the child had been reported. In case of a reported child, further questions were asked about the perpetrator, the frequency, type and severity of the abuse. The contact person was also asked whether the report had been further investigated.

#### Secondary outcome measures

##### Number of risk factors for child abuse

The number of risk factors present at baseline and two years after birth will be measured by self report by using the following questionnaires:

**1. Demographic factors **such as age, ethnicity, whether women received financial help or housing assistance from the government. Women were also asked whether the pregnancy was wanted. This questionnaire was translated from the registration forms used in the NFP.

**2. Depression **was measured by using the Edinburgh Post Natal Depression Scale (EPDS). The EPDS is effective in the detection of depression symptoms and can be used during pregnancy [49]. A total score higher than 13 indicates that the participant is suffering from depression and a score of 10 or higher indicates that the participant is possibly suffering from depression.

**3. Domestic violence **was addressed through detailed questions about violence in the past and the present by spouses or significant others.

**4. Substance use **was addressed by asking the women whether they smoked cigarettes, drank alcohol or used other drugs.

#### Sample size

Sample size calculation was based on finding effect in smoking cessation at the time of birth, 12 months and 24 months post partum. The numbers in the formula were based on findings from the effect study of the NFP[50]. In order to detect an average improvement of decreasing smoking by 4 cigarettes a day with a standard deviation of 8 cigarettes, a power of 80% and an alpha of 5% were used. This resulted in a sample size of 57. Given the fact that 25% of all women smoke at the start of the pregnancy, 228 participants in the control group and 228 participants in the intervention group should at least complete the pregnancy-component.

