#### Primary outcome measures

##### Smoking cessation

Specific questions were about numbers of cigarettes smoked at the gestational window of 16 to 28 weeks and during 32 weeks of pregnancy and 2 months postnatal. Smoking cessation by participant self report was measured at 32 weeks of pregnancy and 2 months postnatal.

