#### Analyses

The effectiveness of the VoorZorgprogram compared to care as usual will be analyzed with different statistical methods, using intention to treat analyses. Logistic Regression analyses will be used for comparing proportions between the intervention group and control group (smoking cessation, birth outcome, domestic violence and child abuse). Linear Regression analyses will be used for comparing means between the intervention and control group (numbers of cigarette smoked, birth weight, gestational age, child development and number of risk factors for child abuse). Multilevel analyses will be used for analyzing longitudinal data. The multilevel and regression analyses using the (longitudinal) data as dependent variables were adjusted for possible confounders and were also checked for possible effect modification like age and ethnicity.

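### The stated 80% power is computed for cigarettes per day but attributed to smoking cessation, at time points where neither primary smoking outcome is defined; the inputs also give 63 smokers per arm, not 57

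*Protocol article*

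**What the plan says.** All references are to the protocol article.

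- **Sample size**, outcome and timing: "Sample size calculation was based on finding effect in smoking cessation at the time of birth, 12 months and 24 months post partum".
- **Sample size**, inputs: "decreasing smoking by 4 cigarettes a day with a standard deviation of 8 cigarettes", with "a power of 80% and an alpha of 5% were used". Whether alpha is one- or two-sided is not stated. The result: "This resulted in a sample size of 57".
- **Sample size**, scaling: "Given the fact that 25% of all women smoke at the start of the pregnancy", at least 228 women per arm should complete the pregnancy component.
- **Primary outcome measures, Smoking cessation**: "Smoking cessation by participant self report was measured at 32 weeks of pregnancy and 2 months postnatal". The same paragraph lists the number of cigarettes smoked, at 16 to 28 weeks, 32 weeks and 2 months postnatal.
- **Outcome Measures**: interviews take place at 16 to 28 weeks, 32 weeks, and 2, 6, 12 and 24 months. None is at birth.
- **Analyses**: "Logistic Regression analyses will be used for comparing proportions between the intervention group and control group (smoking cessation" and other binary outcomes); "Linear Regression analyses will be used for comparing means between the intervention and control group (numbers of cigarette smoked" and other continuous outcomes). The approach is intention to treat, with adjustment for possible confounders that are not named.

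No quit rate, odds ratio or calculation for a binary outcome appears anywhere.

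**The concern.** The Sample size section names one outcome and computes another. A mean difference of 4 cigarettes with an SD of 8 says nothing about the power to detect a difference in the proportion who stop. The time points differ as well: birth, 12 and 24 months are not where either primary smoking outcome is defined.

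This is the only power statement in the article. A reader who takes it at face value could read a null cessation result as coming from a trial with 80% power for cessation, when a moderate difference might well have been missed. The figure of 57 also looks too low for its own inputs, so the stated power may not hold even for the quantity that was calculated.

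**Working it through.** **1. What 57 counts.** 57 / 0.25 = 228, the stated number per arm. So 57 is smokers per arm. This is inferred from the arithmetic; the text does not say it.

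**2. Reproducing 57.** Inputs: difference 4, SD 8, power 80%, alpha 5%. Normal formula: n per arm = 2 × SD² × (z_alpha + z_power)² / difference².

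- Two-sided: 2 × 64 × (1.960 + 0.842)² / 16 = 62.8, so 63 per arm, or 63 / 0.25 = 252 women per arm.
- One-sided: 2 × 64 × (1.645 + 0.842)² / 16 = 49.5, so 50 per arm.
- t-test versions give 64 and 51.

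None gives 57. A three-measurement formula reaches 57 only at a within-woman correlation of about 0.86, and baseline adjustment only at a correlation of about 0.30. Neither correlation is stated.

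**3. Power for cigarettes per day with 57 per arm.** Standard error = 8 × √(2/57) = 1.499; 4 / 1.499 = 2.669; 2.669 − 1.960 = 0.709; power = 76% two-sided (85% one-sided).

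**4. Power for cessation with 57 smokers per arm.** Two proportions, two-sided 5%, pooled variance under the null. The article gives no quit rates, so all of these are assumed.

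| Control vs intervention | Power, 57 per arm |
|---|---|
| 5% vs 15% | 43% |
| 10% vs 20% | 32% |
| 15% vs 30% | 48% |
| 20% vs 30% | 23% |
| 20% vs 40% | 65% |

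Intervention quit rate needed for 80% power:

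| Control | Intervention | Difference in points |
|---|---|---|
| 5% | 23% | 18 |
| 10% | 31% | 21 |
| 15% | 38% | 23 |
| 20% | 44% | 24 |
| 30% | 56% | 26 |

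For 10% vs 20%, 80% power needs 199 smokers per arm, or 199 / 0.25 = 796 women per arm.

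**5. Sensitivity to the smoking share.** With an assumed 50% smokers, 228 × 0.5 = 114 per arm. Power is then 56% for 10% vs 20%, 41% for 20% vs 30%, 78% for 15% vs 30% and 91% for 20% vs 40%.

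**6. Cigarettes per day in all 228 women per arm, unadjusted.** The effect becomes 0.25 × 4 = 1 cigarette. Variance per arm = 0.25 × 64 + 0.25 × 0.75 × (smoker mean)², with the intervention mean 4 lower. For an assumed control-smoker mean of 8, the variances are 28 and 19, the standard error is √(47/228) = 0.454, and power is 60%. For means of 10 and 12 it is 51% and 43%. With baseline smoking status as a covariate, simulation of the same scenario gives about 75% for all three means, close to the smokers-only figure.

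**7. Time points.**

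| | Sample size section | Primary smoking outcomes |
|---|---|---|
| Cessation | birth, 12, 24 months | 32 weeks, 2 months |
| Cigarettes per day | not separately named | 16 to 28 weeks, 32 weeks, 2 months |

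There is no overlap.

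**The case against.** Several stronger readings are tempting, and the document does not support them.

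- **That yes/no cessation is the one outcome that decides the trial or the smoking question.** It is one of five primary domains. Cigarettes per day stands under the same primary heading with its own linear regression, so the quantity in the formula is measured and analysed. That is right, but it does not supply a power statement for cessation, and the count is still not defined at birth, 12 or 24 months.
- **That smoking is not asked about after 2 months.** It is: the secondary risk-factor count includes a smoking question at two years. That gives smoking status inside a secondary measure, not a primary smoking outcome at that time.
- **That never-smokers will dilute the smoking analyses.** Intention to treat means analysed as randomised; it does not say that women who never smoked enter these models. The scaling step suggests a smoker subset, an article may leave the analysis set to a fuller document, and adjustment for baseline smoking would recover nearly all the loss. The dilution is a conditional risk.
- **That cessation is shown to be badly underpowered.** The power figures rest on assumed quit rates and on 25% smokers. Smoking is one of the qualifying risk factors, so the enrolled share may be higher. At an assumed 50%, larger effects are adequately or nearly adequately powered. A 10-point difference from a control rate of 10% or 20% still is not.

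What remains untouched is the contradiction between sections and the figure of 57.

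**Conclusion.** The point holds in this form. The 80% power belongs to a difference in mean cigarettes per day among smokers, not to cessation, and is attached to time points at which neither primary smoking outcome is defined. This follows from the article's own text and needs no assumption.

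The arithmetic is also off. The stated inputs need 63 smokers per arm two-sided; 57 gives about 76%. This assumes a two-sided alpha and a single comparison of two means. One-sided, 57 would exceed the 50 needed, so it matches neither reading.

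The size of the shortfall for cessation is conditional: about 23% to 43% power for a 10-point difference at assumed control rates of 5% to 20%, with 57 smokers per arm. The practical consequence is that a null cessation result should not be presented as coming from a trial with 80% power for that outcome.

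**What to change.** 1. Restate the Sample size section as a calculation for mean cigarettes per day among smokers, with its power of about 76% two-sided at 57 smokers per arm, or give the unstated assumption that produced 57.
2. State the cessation difference detectable with the number of baseline smokers actually enrolled, with the assumed control quit rate and a range around it.
3. Align the time points of the power statement with the primary smoking outcomes (32 weeks and 2 months), or delete birth, 12 and 24 months from its basis.
4. Analyse both smoking outcomes as randomised, either among women smoking at the 16 to 28 week interview or in all women with baseline smoking as a covariate, and say which.

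Cessation need not lose its primary status.

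**Cost.** Recruitment is complete, but the article describes the comparisons as still to be done. The changes are to wording, the analysis set and one short calculation; no new data are needed. The stated power becomes less favourable. Restricting to baseline smokers also leaves out women who stopped before the baseline interview, whereas the 25% figure refers to the start of pregnancy.

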#### Randomization

A total of 460 women were included and randomized in strata by region and ethnicity into a control or intervention group by a researcher of the VU University medical center. Randomization was made blind by using a computer-generated list of random numbers (0, 1) in software SPSS 14.0 [51]. The researcher then informed the VoorZorg nurse about allocation. 237 women were assigned to the intervention group and were visited by trained VoorZorg nurses. 223 women were allocated to the control group and received the care as usual. A flow-chart of the RCT is shown in Figure 2. Women who lived in the same house as another participant of VoorZorg were not randomized but assigned into the same treatment group to prevent contamination. This was relevant for one respondent who was assigned to the intervention group without randomization.

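### The sample size of 57 smokers per group cannot be reproduced from its stated inputs; a standard two-group comparison needs 63–64, and 57 gives about 75–76% power

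*Protocol article*

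**What the plan says.** The Sample size section of the protocol article ties the calculation to smoking at birth and at 12 and 24 months after it, with planning numbers taken from the American effect study of the parent programme. It sets out to "detect an average improvement of decreasing smoking by 4 cigarettes a day with a standard deviation of 8 cigarettes", and adds that "a power of 80% and an alpha of 5% were used". The result follows at once: "This resulted in a sample size of 57". The section then scales up: "Given the fact that 25% of all women smoke at the start of the pregnancy", it requires that "228 participants in the control group and 228 participants in the intervention group should at least complete the pregnancy-component".

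It gives no sidedness, correlation, covariate adjustment or allowance for dropout. The Randomization section reports 460 women, 237 of them assigned to the intervention, and "223 women were allocated to the control group and received the care as usual". The Design section gives the allocation ratio as 1:1.

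**The concern.** This is the only sample size and power statement in the article, and it presents 57 as the outcome of the inputs it lists. An SD of 8 and a difference of 4 give a standardised difference of 0.5, for which the usual two-group requirement at 80% power and two-sided 5% is above 60 per group.

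If 57 is simply too small, a null smoking result would be read as coming from an 80%-powered comparison when the plan's own inputs do not support that. If a more elaborate formula was used, the reader cannot tell which one, or whether it matches the outcome to be analysed.

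**Working it through.** **Inputs, all from the Sample size section unless noted.** Difference 4; SD 8; power 80%; alpha 5% (two-sided assumed, since sidedness is not stated); smoking share 25%; 228 completers per arm. Allocated: 237 and 223 (Randomization).

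**Step 1. What 57 refers to.** 57 / 0.25 = 228, exactly the per-arm requirement, so 57 is smokers per group. This scaling step reproduces. Read as a total, 57 would give only about 46% power.

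**Step 2. Required number per group.** n = 2 × (z₀.₉₇₅ + z₀.₈₀)² × (SD/difference)² = 2 × (1.960 + 0.842)² × (8/4)² = 62.8, so 63. The t-test version gives 63.8, so 64. The stated 57 is 6 to 7 short, about 10%, which is more than rounding. At 25% smokers the arms become 63 / 0.25 = 252 or 64 / 0.25 = 256 women (504 or 512 in total), against 2 × 228 = 456 stated.

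**Step 3. Power at 57 per group.** Normal approximation: 0.5 × √(57/2) − 1.960 = 0.709, and Φ(0.709) = 76.1%. By t-test, 75.4%. The difference detectable with 80% power is 8 × 2.802 / √28.5 = 4.2 cigarettes a day.

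**Step 4. Other readings without new inputs.**
- One-sided 5%: 2 × (1.645 + 0.842)² × 4 = 49.5, so 50 (51 by t-test).
- One-sample or paired comparison: 34.
- Bonferroni correction over three time points: 84.

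None gives 57.

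**Step 5. Readings that add an unstated input.**
- Mean of three measurements, 62.8 × (1 + 2ρ)/3: 56.5 at ρ = 0.85, and 57.0 at ρ about 0.86.
- Mean of two measurements, 62.8 × (1 + ρ)/2: 56.5 at ρ = 0.80.
- Baseline adjustment, 62.8 × (1 − r²): 57.1 at r = 0.30.

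Each lands on about 57, but none of these correlations appears in the article.

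**Step 6. Time points.** The Sample size section names birth, 12 months and 24 months. The Smoking cessation section, under primary outcomes, defines cessation at 32 weeks of pregnancy and 2 months after birth. The measurement schedule under Outcome Measures has visits at 12 and 24 months but none at birth. Smoking at two years is asked as part of the secondary count of risk factors. The time points behind the calculation are therefore not those of the primary smoking outcome.

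**Step 7. The enrolled sample.** At 25% smokers, 237 × 0.25 = 59.25 and 223 × 0.25 = 55.75. Unadjusted t-test power is 75.7% before attrition. At assumed shares of 30% and 40%, the same arms give about 83% and 92%.

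**Step 8. The control arm.** 228 − 223 = 5 women below the completer minimum before any dropout. The effect on power is negligible: 75.7% with the actual split, against 75.4% for 57 per group.

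**The case against.** The best defence is that the section does not describe a single-time, unadjusted comparison. It names three time points and draws its numbers from an outside study, and the Analyses section plans multilevel models for longitudinal data with adjustment for confounders. A condensed article may omit a correlation that the full protocol contains. A baseline correlation of about 0.30 is modest and would be enough, and cigarette numbers are recorded at baseline. This part stands: 75–76% is the power of the standard comparison, not a proven property of the planned analysis. It does not rescue the figure, because the article says its listed inputs yielded 57, and they do not.

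A reader might also infer that 57 can come only from averaging three highly correlated measurements. Step 5 shows two other routes, so the documents do not support that.

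A third objection is that the 25% describes women in general. The Study population section lists smoking during pregnancy among the risk factors that qualify a woman, so the enrolled share may be higher. That also stands, and it bars any fixed statement about realised power.

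Finally, total enrolment of 460 exceeds 456, and the uneven split arose in allocation. That is fair, and it makes the control-arm shortfall a matter of disclosure.

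**Conclusion.** The stated sample size does not follow from the stated inputs. Under a two-sided 5% two-group comparison of means, 80% power needs 63–64 smokers per group (252–256 women per arm if 25% smoke). The stated 57 gives 75.4–76.1% power, or 80% for 4.2 instead of 4 cigarettes a day. The gap is 4 to 5 power points. It closes only if the article supplies a formula and correlation that it does not now state.

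It is tempting to conclude that the trial is underpowered. The documents do not support that: the number of enrolled smokers is not given, and power with the allocated arms is about 76% at 25% smokers but about 83% at 30% and 92% at 40% (assumed shares, no attrition). Nor does the shortfall of 5 control women matter much for power, although it does miss the plan's own per-arm minimum.

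This is a correction to reporting. No estimate, test or outcome changes.

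**What to change.** 1. Either correct 57 to 63–64 and 228 to 252–256, or state the repeated-measures or baseline-adjusted formula and the correlation used.
2. If a repeated-measures formula was used, reconcile its time points (birth, 12 and 24 months) with those of the primary smoking outcome (32 weeks and 2 months after birth).
3. Restate the power of the enrolled sample from the actual number of baseline smokers in each arm, in place of the 25% for all women, and say whether attrition is included. Until that is done, about 76% at 25% smokers is the figure for the unadjusted comparison before attrition.
4. Add one sentence disclosing that the control allocation of 223 lies below the minimum of 228 completers, with little effect on power.

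No further enrolment or design change is needed. The cost is a few sentences and one recalculation. The stated power may become slightly less favourable, or more favourable if more than 25% of the women smoked.

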## Background

### Adverse events

The Adverse Childhood Experience Study concluded that living in poverty combined with other risk factors affects a person's physical and psychosocial health from childhood to adulthood. Moreover, even next generation(s) experience the same consequences as their parents suffered; they are all trapped in a vicious circle[1].

Low SES affects the child, even before birth. The unborn child is at risk of adverse pregnancy outcomes because of the negative health patterns of the parents. For example, women of low SES use substances during pregnancy more frequently than other women, and maternal substance use during pregnancy contributes to premature birth and low birth weight and is strongly associated with morbidity and mortality of the newborn as well as in childhood [2-6]. Having psychosocial problems during pregnancy leads to many complications, such as spontaneous abortion or preterm delivery; it also increases the chances that a child will later develop conduct problems [7-9]. The lack of structure in the life of the children also increases their risk of displaying conduct problems and engaging in criminal activities. The low SES living area of the children is often unsafe; in this environment, children are more likely to experience injuries [10]. Child abuse is more common among these families. The consequences of child abuse are high: abused children have more psychosocial problems, low self esteem and morbidity [11]. In addition, abused children are more likely to engage in negative health behavior and criminal behavior when they get older [12]. Beyond these problems, the children are at risk of becoming a perpetrator of abuse themselves in the future [13-15].

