#### Study population

460 women were selected with a two-stage selection procedure from the year 2006 to 2009. The selection procedure is described more in detail elsewhere ([name], [name], [name], [name], [name], [name], [name], unpublished data). During the first stage professionals like General Practioners, midwifes, gynecologists and street corner workers recruited women in 20 different regions in the Netherlands based on the following criteria: Age below 26 years, low educational level (primary school or primary school and secondary school on a low level), pregnant with her first child, maximum 28 weeks of gestation, and understanding the Dutch language at a minimum level. During the second stage of the selection procedure the women were interviewed by VoorZorg nurses on several risk factors ((1) no or little social support, (2) a history of violence or abuse, (3) or still in a situation of domestic violence or neglect, (4) psychological problems, (5) financial problems, (6) unemployed or (7) housing problems, (8) alcohol problems, smoking or using drugs during pregnancy, or (9) having a non-realistic approach about motherhood) with the use of an inventory. Women who had at least one risk factor were included in the study. Furthermore, women had to understand the aim of the program and had to have the intention to complete the entire program. In addition, they were willing to participate in the study and be randomly assigned to an intervention or control group. Women who were found eligible for the study then signed, after the explanation of the study by the VoorZorg nurses, a written informed consent form. The participants were able to withdraw from the study at any time.

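### The 228-per-arm target uses a general-population smoking rate that does not describe the enrolled women; the error is probably on the conservative side, and underpowering is not shown

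*Protocol article*

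**What the plan says.** In the protocol article, Sample size, the trial is sized on cigarettes smoked. The aim is to "detect an average improvement of decreasing smoking by 4 cigarettes a day with a standard deviation of 8 cigarettes", and "a power of 80% and an alpha of 5% were used". The article continues: "This resulted in a sample size of 57". This number is then scaled up to a recruitment target per arm: "Given the fact that 25% of all women smoke at the start of the pregnancy, 228 participants in the control group", with the same number in the intervention group, counted as women who complete the pregnancy component.

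Study population defines who is enrolled: first-time mothers under 26, with low education, at no more than 28 weeks of gestation. A second stage screens on nine risk factors, one of which reads "8) alcohol problems, smoking or using drugs during pregnancy". Any one of the nine is enough: "Women who had at least one risk factor were included in the study".

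The Background, under Adverse events, states that "women of low SES use substances during pregnancy more frequently than other women". Under Smoking cessation, the first smoking question concerns "numbers of cigarettes smoked at the gestational window of 16 to 28 weeks".

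**The concern.** The smoking share is the only link between 57 and 228, so the target is inversely proportional to it. The share used belongs to women in general at the start of pregnancy. The women enrolled differ from that group in three ways:

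- They are selected on youth and low education, and the article itself associates low SES with more substance use.
- Smoking is one way to satisfy the risk screen, so a smoker meets that screen automatically, while a non-smoker needs another factor.
- Their smoking is first counted at 16 to 28 weeks, when some women who smoked at the start of pregnancy may have stopped.

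The first two push the share above 25% and the third pushes it down. Smoking is listed first among the primary outcomes and is the only one with a sample size calculation. If the share is wrong, the number of smokers available and the power for this outcome are not what the article states. A reader of a null smoking result then could not judge it against the stated 80%.

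**Working it through.** **Inputs.** From Sample size: difference 4 cigarettes a day, SD 8 (standardised effect 4/8 = 0.5), power 80%, alpha 5% (sidedness not stated), 57 smokers (implicitly per arm), share 25%. From Randomization: 237 intervention, 223 control. The smoking share p among the enrolled women is not in the document, so it is varied over an assumed range.

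**1. The plan's own scaling step.** 57 / 0.25 = 228. This reproduces exactly and confirms that the 25% alone turns 57 into 228.

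**2. The 57 itself.** Smokers per arm = 2 × [SD × (z for alpha + z for power) / difference]².

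- Two-sided: 2 × [8 × (1.960 + 0.842) / 4]² = 62.8, so 63; with the t distribution 63.8, so 64.
- One-sided: 49.5, so 50; with the t distribution 50.2, so 51.

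Neither gives 57. With 57 smokers per arm the two-sided power is about 75% (t) to 76% (normal approximation). This gap exists even if 25% is exactly right, so it must be kept apart from the question about the smoking share.

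**3. Sensitivity to the smoking share.** Women needed per arm = 57/p, or 64/p with the number that the stated inputs require (both rounded up). Power is for a two-sided 5% t-test with effect 0.5 and 223p and 237p smokers in the two arms, before any dropout.

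| Assumed p | 57/p | 64/p | Smokers, control / intervention | Power |
|---|---|---|---|---|
| 20% | 285 | 320 | 45 / 47 | 66% |
| 25% | 228 | 256 | 56 / 59 | 76% |
| 28% | 204 | 229 | 62 / 66 | 80% |
| 30% | 190 | 214 | 67 / 71 | 83% |
| 40% | 143 | 160 | 89 / 95 | 92% |
| 50% | 114 | 128 | 112 / 119 | 97% |

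The share at which 228 women per arm contain 64 smokers is 64/228 = 28%. Above that, the planned effect has at least 80% power before dropout; below it, less.

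**4. Effect of the risk screen.** Suppose a fraction f of women who pass stage 1 also pass the risk screen. Since every smoker passes, the share of smokers among those passing equals the stage-1 share divided by f. For illustration, a 25% stage-1 share becomes 0.25/0.8 = 31% if f is 80%, and 0.25/0.7 = 36% if f is 70%. Both values of f are assumptions. With nine broad alternatives f could be close to 1, and the enrichment would then be negligible.

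**The case against.** The strongest reply is that no harm has been shown. The influences that the document supports, low SES and the entry rule, raise the smoking share and make 228 more than enough. A lower share rests on early quitting, for which there is no figure. This stands, and it decides the direction in which the point can be put.

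A reader might infer from the 76% at 25% that the smoking rate has left the trial underpowered. The document does not support that. The 76% comes from using 57 where about 64 are needed, and it would be there with a perfectly chosen rate.

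A reader might also infer that the enrolled share cannot be below the stage-1 share. That holds for the risk screen only. Women also had to understand the aim of the programme, intend to complete it and accept randomisation, and smokers may have differed at those steps. Smoking is also part of a combined item with alcohol and drugs, and it is not required for entry.

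The timing argument is limited too. The article asks about cigarettes at 16 to 28 weeks but does not say that the analysis set is the women smoking at that visit.

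Two further replies carry less weight. A fuller protocol may justify the 25%, and the phrase about all women could be read as all participants. The article, however, attributes the figure to women in general at the start of pregnancy, and the difference in timing would remain on either reading.

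Finally, a sample size rationale should not be rewritten after recruitment. That is fair, and it is met by keeping the planning figure and adding the observed one beside it.

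**Conclusion.** The point holds in a limited form. The 228-per-arm target rests on a smoking share for a different population and an earlier time point than the women and the measurement in this trial. By the article's own account the share is probably too low, so the target is probably conservative; early quitting could offset this by an unknown amount. The net direction is therefore not established.

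Over assumed shares of 20% to 50%, power for the planned effect runs from about 66% to 97%, and it crosses 80% at about 28%. These figures assume two-sided testing, a comparison of means among smokers with SD 8, and no dropout. They are a range and not an estimate, because the enrolled share is not given. The stated 80% cannot be confirmed for the enrolled women, but it is not shown to be missed because of the smoking share. The mismatch between 57 and about 64 is a separate arithmetic fault in the same section.

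**What to change.** In Sample size, keep the 25% as the original planning assumption and label it as a general-population figure for the start of pregnancy. Beside it, report the number and proportion of smokers in each arm from the cigarette count at 16 to 28 weeks. That count is a better source than the stage-2 inventory, whose item combines smoking with alcohol and drugs and refers to pregnancy in general. Then restate the power for 4 cigarettes, SD 8 and two-sided 5% with those numbers of smokers. This uses the planned effect, so it is not power calculated from the observed result. State separately that these inputs require about 64 smokers per arm two-sided, or give the method and sidedness behind 57.

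The cost is a few sentences and one tabulation of data that the article says were collected. Enrolment need not change. The restated power may come out above or below 80%.
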